# Evaluation of the telemedical health care network “SAFE BIRTH” for pregnant women at risk, premature and sick newborns and their families: study protocol of a cluster-randomized controlled stepped-wedge trial

**DOI:** 10.1186/s12913-024-10667-z

**Published:** 2024-02-14

**Keywords:** Perinatal care, Telemedicine, Stepped-wedge, Evaluation, Health services research, Implementation, Non-metropolitan regions, Study protocol

## Abstract

**Background:**

The Perinatal Center of the University Hospital Carl Gustav Carus Dresden has initiated the telemedical healthcare network “SAFE BIRTH” to coordinate and improve specialized care in non-metropolitan regions for pregnant women and newborns. The network incorporates five intervention bundles (IB): (1) Multi-professional, inter-disciplinary prenatal care plan; (2) Neonatal resuscitation; (3) Neonatal antibiotic stewardship; (4) Inter-facility transfer of premature and sick newborns; (5) Psycho-social support for parents. We evaluate if the network improves care close to home for pregnant women, premature and sick newborns.

**Methods:**

To evaluate the complex healthcare intervention “SAFE BIRTH” we will conduct a cluster-randomized controlled stepped-wedge trial in five prenatal medical outpatient offices and eight non-metropolitan hospitals in Saxony, Germany. The offices and hospitals will be randomly allocated to five respectively eight sequential steps over a 30-month period to implement the telemedical IB. We define one specific primary process outcome for each IB (for instance IB#1: “*Proportion of patients with inclusion criterion IB#1 who have a prenatal care plan and psychosocial counseling within one week”*). We estimated a separate multilevel logistic regression model for each primary process outcome using the intervention status as a regressor (control or intervention group). Across all IB, a total of 1,541 and 1,417 pregnant women or newborns need to be included in the intervention and control group, respectively, for a power above 80% for small to medium intervention effects for all five hypothesis tests. Additionally, we will assess job satisfaction and sense of safety of health professionals caring for newborns (questionnaire survey) and we will assess families’ satisfaction, resilience, quality of life and depressive, anxiety and stress symptoms (questionnaire surveys). We will also evaluate the cost-effectiveness of ”SAFE BIRTH” (statutory health insurance routine data, process data) and barriers to its implementation (semi-structured interviews). We use multilevel regression models adjusting for relevant confounders (e.g. socioeconomic status, age, place of residence), as well as descriptive analyses and qualitative content analyses.

**Discussion:**

If the telemedical healthcare network “SAFE BIRTH” proves to be effective and cost-efficient, strategies for its translation into routine care should be developed.

**Trial registration:**

German clinical trials register. DRKS-ID: DRKS00031482.

## Background

Demographic as well as structural changes in the hospital landscape challenge medical care in many regions of Germany. One of the measures taken to meet these challenges is increasing centralization of specialized care, as successfully done in other countries [1]. Centralization of care requires functioning networks between health professionals in different areas and of different disciplines. Telemedicine can connect health professionals and support the provision of specialized care in non-metropolitan regions. In the field of perinatal care, telemedicine is a feasible method of increasing access to expert care, improving parental and caregiver education, reducing transports and improving quality of care [2].

In Saxony, a federal state of Germany, the Perinatal Center of the University Hospital Carl Gustav Carus Dresden (PC-UKD) has initiated the health care network “SAFE BIRTH” (HCNSB, German: “Versorgungsnetz Sichere Geburt”) together with the largest statutory health insurance fund in this region (AOK Plus) to coordinate and improve specialized care in non-metropolitan regions of Saxony. Recent studies show the need and present structural requirements for telemedical support in perinatal care in this region [3, 4]. The telemedical network HCNSB consists of five intervention bundles:

#1: Multi-professional, inter-disciplinary prenatal care plan for pregnant women and their unborn child.#2: Neonatal resuscitation.#3: Neonatal antibiotic stewardship.#4: Inter-facility transfer of premature and sick newborns.#5: Psycho-social support for parents.

The complex healthcare intervention HCNSB is funded by the Innovation Fund of the Federal Joint Committee (German: Gemeinsamer Bundesausschuss (G-BA)). The G-BA specifies which services in medical care are reimbursed of the statutory health insurance funds (routine care) for more than 73 million insured individuals. New forms of care funded by the G-BA have to show potential for permanent implementation into routine care. The accompanying scientific evaluation examines the effectiveness of the intervention bundles of HCNSB within the existing care structures. The results of the evaluation will play a leading role in the decision which innovations will be reimbursed of the statutory insurance funds.

The evaluation of the HCNSB examines the following hypotheses and qualitative research questions:

Primary hypothesis: The intervention bundles (IB) of the HCNSB improve care close to home compared to current routine care.

Secondary hypotheses:

The IB increase job satisfaction and the feeling of safety of health professionals caring for premature and sick newborns. IB furthermore increase patients’ and families’ satisfaction with care, resilience and quality of life and reduce depressive, anxiety and stress symptoms.The IB are cost-effective from a statutory health insurance (SHI) perspective.

Qualitative research questions:

Which barriers hinder health professionals, pregnant women and families of newborns to use the IB?How do the IB influence the satisfaction and sense of safety of health professionals? How do they influence the patients’ sense of safety?

A cluster-randomized controlled stepped-wedge design (SW-cRCT) was chosen to investigate the hypotheses and research questions. Randomization will be performed at the hospital respectively outpatient office level.

## Methods

The method chapter is based on the SPIRIT reporting guidelines [5].

The Perinatal Center of the University Hospital Carl Gustav Carus Dresden (PC-UKD) coordinates the HCNSB. Five prenatal medical outpatient offices and eight hospitals participate in the project (see Fig. 1). They are members of the Saxony Center for Feto/Neonatal Health. All study sites are listed in the trial registration (DRKS00031482).

**Fig. 1 Fig1:**
[figure not shown]
Locations of study sites of the HCNSB in Saxony (Dresden as location of the coordinating facility in red)

### Eligibility criteria

All patients or newborns meeting the following criteria will be included:

IB#1: Pregnant women with a disorder affecting fetal health (e.g. gestational diabetes) or with a suspicion of a serious disease of the fetus who are cared for on an outpatient basis by a participating prenatal obstetrician,IB#2: Newborns cared for in the delivery room or admitted as inpatients who required resuscitation or intensive care at the participating hospital,IB#3: Newborns admitted as inpatients who receive antibiotic therapy at the participating hospital and/or have a positive microbiologic screening result,IB#4: Premature or sick newborn receiving inpatient care at a participating hospital or the PC-UKD with a suspected need for transfer to the PC-UKD or indication for transfer back close to home,IB#5: Families of newborns hospitalized at a participating hospital for more than 5 days.

The secondary study population consists of outpatient obstetricians and health professionals at the hospitals using IB.

### Intervention bundles (IB) of the health care network “SAFE BIRTH” (HCNSB)

#### Intervention bundle #1: Multi-professional, inter-disciplinary prenatal care plan

In Germany, midwives and outpatient obstetricians care for pregnant women. In the event of any abnormalities, pregnant women are examined by a specialist for prenatal diagnostics. If the suspicion of a fetal abnormality or maternal risk is confirmed, prompt multi-disciplinary and inter-professional planning of further steps is necessary. Currently, the development of an individual care plan is usually done in a specialized perinatal center. This current process is associated with lengthy waiting times and increased health care costs [3]. Psycho-social aspects are often not adequately addressed [3].

IB#1 is aimed at all pregnant women with fetal or maternal abnormalities requiring control at the PC-UKD and consists of the following measures:

The **prenatal tele-consultation** enables the outpatient obstetrician to have an immediate virtual consultation with the expert of the PC-UKD while the pregnant woman is still present.In the **prenatal jour-fixe**, recorded findings are discussed in the virtual room, without the participation of the pregnant woman.Subsequently, the **prenatal care plan** is determined, if necessary with the involvement of other disciplines.In addition, the psycho-social team of the PC-UKD contacts the pregnant woman by telephone, thus ensuring prompt **psycho-social counseling** tailored to the individual characteristics.A virtual **feto-neonatal board meeting** serves to review and adapt the prenatal care plan to current findings during care.

#### Intervention bundle #2: Neonatal resuscitation

Neonatal resuscitation is a rare event. However, immediate and adequate care of infants is a prerequisite to prevent long-term harm. Specialized neonatal expertise is not available at all facilities, and it can take up to an hour for a neonatal expert from a NICU to arrive on scene. For this reason, it is important that on-site pediatricians have the immediate ability to access the neonatal experts’ support via telemedicine. In some cases, this may even eliminate the need for a neonatologist to travel to the hospital or to transfer the newborn [3].

IB#2 is specifically designed to ensure **immediate availability of neonatal expertise** during neonatal resuscitation. The participating hospital receives **telemedical support** from the neonatology department of the PC-UKD directly after the call. If needed, a neonatal transport can be arranged in parallel and the neonatologist on route can stay informed about the current status of the resuscitation via push messages. In the follow-up of the supported resuscitation, a structured debriefing takes place to optimize the cooperation and to enable quality assurance of IB#2.

The goal is to **reduce neonatal transports** and **improve neonatal care** in critical situations.

#### Intervention bundle #3: Neonatal antibiotic stewardship

Antibiotics are among the most commonly used medications in neonatal units due to the high morbidity and mortality due to neonatal infections. Antibiotic stewardship has been shown to improve rational antibiotic use [6], but the specific expertise in neonatal infectious disease is not available in every institution.

IB#3 ensures appropriate consultation with a pediatric infectiologist at the PC-UKD. If antibiotic treatment is started for a newborn at a participating hospital or if an abnormal microbiological finding is detected, a telemedical infectiology consultation is conducted within 48 h with the aim of recommending an individualized antibiotic therapy.

This is intended **to avoid overtreatment** when antibiotic therapy has already begun or in advance.

#### Intervention bundle #4: Inter-facility transfer of premature and sick newborns

Once the child is stable and no longer needs the highly specialized neonatal care, it is the aim to transfer them close to home. However, this requires a continuous trans-institutional care and that the parents are appropriately prepared [4].

IB#4 provides support to participating hospitals via neonatal tele-consultations and as part of remote neonatal jour fixes. Through the regular exchange of information about neonates who are eligible for transfer close to home, **transfers from the PC-UKD to the hospitals will be promoted and transfers to the PC-UKD will be reduced**. The transfer process to the participating hospitals is accompanied by psycho-social support services and the parents are involved in these joint “remote rounds” in order to reduce uncertainties and enable an optimal flow of information. The jour fixes also serve as quality assurance measure by debriefing children who have already been transferred.

#### Intervention bundle #5: Psycho-social support for parents

The aim of professional psycho-social support in neonatology is to improve parent-child bonding and to optimize medical treatment by helping to organize follow-up and preventive care appointments. The positive effects of these psycho-social support services have been published several times [7, 8]. However, development and implementation of recommended measures require substantial financial, organizational and personnel resources. Notably, the highly specialized staff needed is often not available for the time-consuming counseling work in smaller clinics.

In IB#5, families who stay more than 5 days in the participating hospital receive the offer of telemedical support based on the psycho-social expertise of the PC-UKD. Families are offered virtual parent training, telephone counseling sessions and support in contacting local psycho-social services.

Figure 2 provides an overview of all five IB of the HCNSB.

**Fig. 2 Fig2:**
[figure not shown]
The five intervention bundles (IB) of HCNSB

### Technical implementation of the intervention bundles (IB)

Eckart et al. [4] describe the details of the basic technical implementation. The project coordinator decided to use the JOIN messenger application (Allm Inc., Tokyo, Japan), which is certified as a medical device. Special attention was paid to pseudonymized, GDPR compliant data use during implementation. It turned out that the implementation by means of mobile devices is the most suitable for most IB, since the audio and video capabilities of modern devices are sufficient for this. The JOIN web application seems most appropriate for IB#1, where ultrasound images or videos are transmitted via HDMI converter, and in other IB when additional devices are necessary, for example for larger conferences.

### Outcomes

The outcomes refer to the interventions of the intervention bundles IB#1 to IB#5. Primary process outcomes are (data sources in brackets are described in more detail in chapter “Data management and collection”):

IB#1: Proportion of patients with inclusion criterion IB#1 who have a prenatal care plan with a multi-professional recommendation for postnatal care and psychosocial counseling within one week (data source: project database),IB#2: Proportion of neonates with inclusion criterion IB#2 for whom neonatology expertise is available in the delivery room < 15 min postnatally (including telemedicine, if applicable) (data source: project database),IB#3: Proportion of newborns with inclusion criterion IB#3 in which antibiotic could be discontinued within 48 h (in case of CrP, IL-6 negative and negative blood culture) or antibiotic therapy for 6 days (in case of pos. blood culture) with antibiotic was performed according to resistogram (data source: project database),IB#4: Proportion of newborns cared for at the UKD from the region (according to zip code list) who were finally discharged from a hospital close to home (data source: project database),IB#5: Proportion of patients with inclusion criterion IB#5 who received at least one psychosocial support service (data source: project database).

Secondary outcomes are listed in Table 1.

**Table 1 Tab1:** Secondary outcomes and related data sources

Intervention bundle	Secondary outcome	Data source

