### Assignment of interventions

The decision whether a newborn/patient is assigned to the intervention or control group depends on the time of inclusion. If the recruiting facility is in the control phase, the patient or newborn is assigned to the control group, otherwise to the intervention group. There is no blinding. The order in which the recruiting facilities enter the intervention phase is randomized. Figure 3 illustrates the allocation of clinics and prenatal medical outpatient offices to the intervention time points defined within the 30-month observation period.

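### The IB#4 primary outcome counts only newborns treated at the PC-UKD, a group whose membership the intervention aims to change, and newborns first included there have no stated phase or cluster

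*Protocol article*

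**What the plan says.** All references are to the protocol article.

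- **Outcomes.** The IB#4 primary outcome is the "Proportion of newborns cared for at the UKD from the region (according to zip code list) who were finally discharged from a hospital", meaning one near home. For IB#1, #2, #3 and #5 the denominator is everyone who meets that bundle's inclusion criterion; IB#4 is the exception.
- **Eligibility criteria.** IB#4 admits a "Premature or sick newborn receiving inpatient care at a participating hospital or the PC-UKD with a suspected need for transfer to the PC-UKD". It also admits newborns for whom transfer back is indicated.
- **Intervention bundle #4.** The stated aim is that "transfers from the PC-UKD to the hospitals will be promoted and transfers to the PC-UKD will be reduced". The section on bundle #2 also names fewer neonatal transports as a goal and says that remote support may make a transfer unnecessary.
- **Randomised units.** Abstract, Methods: "The offices and hospitals will be randomly allocated to five respectively eight sequential steps over a 30-month period". The Methods section says "The Perinatal Center of the University Hospital Carl Gustav Carus Dresden (PC-UKD) coordinates the HCNSB" and names the five offices and eight hospitals separately as participants.
- **Recruitment and allocation.** Sample size and recruitment names the participating offices and hospitals as recruiters. Assignment of interventions says: "If the recruiting facility is in the control phase, the patient or newborn is assigned to the control group, otherwise to the intervention group".
- **Data analysis.** Each primary outcome gets a logistic multilevel model with the facility's phase as exposure and a random intercept per institution.

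**The concern.** There are two separate problems.

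First, treatment at the PC-UKD is decided after the hospital's phase is set, and the network is meant to make it less frequent. The outcome is then compared between two differently selected groups of newborns, and randomisation of the hospitals does not protect that comparison. A random intercept does not restore it. A newborn kept at the local hospital and discharged there is a plain success for the primary hypothesis on care close to home, yet contributes nothing to this outcome.

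Second, eligibility allows inclusion at the PC-UKD itself, for example of a newborn awaiting transfer back. The PC-UKD has no randomised step, so the allocation rule gives such a newborn no clear phase, and no randomised hospital is named as its cluster. Read literally, the word 'otherwise' in the rule would put all of them in the intervention group, including those from calendar time when their home hospital was still in the control phase.

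At stake is one of five confirmatory tests in an evaluation that, according to the Background, will weigh heavily in the reimbursement decision.

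**Working it through.** **What can be reproduced.** The plan gives 1,417 control and 1,541 intervention participants over all bundles, with no split, rates or intra-cluster correlation. There is no IB#4 figure to reproduce, and the total is not disputed here.

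**Step 1: selection into the denominator.** All inputs are assumed. Let m be the share of PC-UKD newborns, in control conditions, belonging to the type whose transfers can be avoided; f the fraction of those transfers avoided; a their probability of final discharge close to home after PC-UKD care; and b that probability for the rest. Back-transfer practice is held unchanged.

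- Control proportion: c = m·a + (1 − m)·b
- Intervention proportion: (c − m·f·a) / (1 − m·f)
- Shift: −m·f·(a − c) / (1 − m·f)
- Change in a group fixed before transfer, counting each avoided transfer as discharged close to home: + m·f·(1 − a)

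| m | a | b | f | Control | Intervention | Shift (points) | Fixed-group change (points) |
|---|---|---|---|---|---|---|---|
| 0.5 | 0.8 | 0.3 | 0.3 | 55.0% | 50.6% | −4.4 | +3.0 |
| 0.6 | 0.8 | 0.3 | 0.5 | 60.0% | 51.4% | −8.6 | +6.0 |
| 0.5 | 0.6 | 0.5 | 0.3 | 55.0% | 54.1% | −0.9 | +6.0 |
| 0.5 | 0.6 | 0.6 | 0.3 | 60.0% | 60.0% | 0 | +6.0 |
| 0.5 | 0.3 | 0.8 | 0.3 | 55.0% | 59.4% | +4.4 | +10.5 |

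First row in full: c = 0.5 × 0.8 + 0.5 × 0.3 = 0.55; intervention (0.55 − 0.15 × 0.8) / 0.85 = 0.43 / 0.85 = 0.506; fixed group 0.43 + 0.15 = 0.58. The denominator shrinks by 15%.

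Over m = 0.4 to 0.6, a = 0.6 to 0.8, b = 0.3 to 0.6 and f = 0.1 to 0.5, with a at least as large as b, the shift runs from 0 to −8.6 points, while the fixed-group share rises by 0.8 to 12 points. If any transfers are avoided, the shift is zero only when a = b. The last row lies outside that range and shows that the sign turns if avoided newborns would have returned less often than the rest, for instance because they would have gone straight home from the PC-UKD.

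For scale: with an assumed equal split over bundles (1,417/5 ≈ 283 and 1,541/5 ≈ 308), ignoring clustering and the Holm correction, power for a 10-point difference is 0.69 to 0.80 for control rates of 30% to 70%. A shift of several points is thus not small beside the effects the trial could detect.

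**Step 2: newborns first included at the PC-UKD.** Assume a share u of the denominator is first included there, half of it in control time with control-level outcomes, and true proportions of 50% and 65%. Sending all of them to the intervention group dilutes the true 15 points to 15/(1 + u):

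- u = 0.25: 15/1.25 = 12.0 points
- u = 0.50: 15/1.50 = 10.0 points
- u = 0.75: 15/1.75 = 8.6 points

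The documents do not give u.

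**The case against.** - **Most of the group may have a phase.** A reader might infer that the whole IB#4 denominator falls outside the allocation rule. The documents do not support this. A newborn included at a participating hospital and then moved to the PC-UKD has a recruiting facility, and so a phase and a cluster. Only those first included at the PC-UKD are unclear.
- **The attribution may be written down elsewhere.** The outcome already uses a zip code list, and Table 1 tracks newborns at the PC-UKD by originating hospital. A zip-to-hospital map may well sit in the full protocol, so its absence from the article is not an error, and one cannot conclude that these newborns are unanalysable as randomised. Such a map would settle the second problem but not the first, because the outcome definition itself restricts the denominator to PC-UKD patients.
- **Transfers are measured.** Table 1 lists postnatal transports and the proportion transferred under IB#2, and transfers of the child under Economic impact for IB#2–5. These would help to show a shrinking denominator. They do not remove the selection from the confirmatory test.
- **The outcome suits one aim.** Return home among PC-UKD patients is a coherent measure of back-transfer, and a real gain there would offset a negative shift. That stands.
- **Large shifts are easy to construct.** If a third of transfers are avoided and those newborns return at 75% against 37.5% for the rest, the proportion drops from 50% to 37.5%. A reader might infer that the outcome will reverse sign. Every input is assumed and back-transfer is held fixed, so reversal is possible but not shown.

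**Conclusion.** The point holds in this form. The IB#4 outcome definition, the IB#4 eligibility criterion and the allocation rule do not fit together. The denominator is selected after randomisation by an event that IB#2 and IB#4 set out to change, and analysing the outcome as written can bias the phase comparison. Neither size nor direction can be fixed from the documents: about 0 to −9 points under the assumed ranges with unchanged back-transfer, zero if the avoided newborns return in the same proportion as the rest, and positive if they return less often. That the avoided newborns are the milder ones is plausible but not stated, and the shrinkage is an intended effect rather than an observed one.

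The phase and cluster gap is confined to newborns first included at the PC-UKD, whose share is not given. No number printed in the article is shown to be wrong.

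**What to change.** 1. **Attribution.** Assign every IB#4 newborn to a randomised hospital: by hospital of birth or origin, or by zip code for those first included at the PC-UKD. Use that hospital as the cluster and take its phase at a date set before the transfer decision, such as birth. Reword the allocation rule to match.
2. **Population.** Analyse the proportion finally discharged from a hospital close to home over a population defined as far as possible before the transfer decision, counting newborns never transferred and discharged locally as successes. Make this either the IB#4 primary outcome with its power restated, or a pre-specified key supporting analysis beside the PC-UKD-only proportion.
3. **Reporting.** Give the number of newborns entering each denominator by phase, so that selection can be seen.

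**Cost.** The attribution needs a zip-to-hospital map and a short amendment. The broader outcome is less specific to back-transfer, and its baseline rate differs from the one assumed for the sample size. Suspected need for transfer is judged without blinding, and tele-consultation could bring more mild cases to notice, so a population resting on that judgement alone could favour the intervention. Inclusion began on 29 January 2023; replacing a primary outcome during an unblinded trial needs a dated justification made without sight of results by phase. The supporting-analysis route avoids replacing the primary outcome.
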